# Effect of anti-obesity agent HSG4112 on overweight and obese patients following 12 weeks of oral treatment: a study protocol for a randomised, double-blind, placebo-controlled, parallel-group, phase 2a clinical trial

**DOI:** 10.3389/fphar.2023.1177539

**Published:** 2023-08-24

**Keywords:** obesity, overweight, weight loss, obesity drug, randomised controlled trial

## Abstract

Background: Glaceum Inc. has proposed HSG4112, a structural analogue of glabridin, as a novel anti-obesity compound. Animal studies and phase I human trials have shown that HSG4112 improves energy consumption, normalises weight, and is safe and drug-resistant. Based on these results, the company plans to conduct a phase 2a clinical trial to determine the safety and efficacy of HSG4112 in overweight and obese patients. Methods: A 16-week randomised, double-blind, placebo-controlled, parallel-group trial will be conducted at five large hospitals in South Korea to assess the safety and efficacy of HSG4112 in overweight and obese patients. Participants who meet the inclusion/exclusion criteria will be assigned a subject number and randomly assigned to one of the four treatment groups (one group receiving a placebo) in a 1:1:1:1 ratio. The study’s primary outcome will be to monitor the change in body weight (kg) from baseline to the end of treatment while monitoring safety and tolerability. Discussion: This trial will evaluate the efficacy and safety of HSG4112 in overweight and obese adults. Upon proving the safety and effectiveness of the newly developed mechanism, it might significantly improve the perception of the product among medical personnel and obese patients. Furthermore, it may aid in managing chronic conditions that require long-term treatment.

**Trial registration:**
ClinicalTrials.gov, identifier [NCT05197556].

## 1 Introduction

Obesity is defined as abnormal or excessive fat accumulation that can adversely affect health (Panuganti et al., 2022). World Health Organization has reported that overweight and obesity increase the risk of non-communicable diseases. In the past 45 years, the rate of increase in obesity has tripled worldwide, with 1.9 billion adults aged 18 years or above being overweight and 650 million classified as obese (Ghaus et al., 2021). Obesity is associated with a high risk of morbidity, disability, and death, with mortality risk similar to that of smoking (Whitlock et al., 2009). Major risk factors for mortality include an increased incidence of cardiovascular events, such as coronary heart disease, hypertension, stroke, type 2 diabetes, and some types of cancer, including breast cancer in postmenopausal women, endometrial cancer, and colon and kidney cancer (Knight, 2011). The risk of these non-communicable diseases increases with increased body mass index (BMI). Moreover, reports show that obesity is positively correlated with an increased risk of morbidity and mortality related to COVID-19 (Singh et al., 2022).

Several studies have confirmed that lifestyle changes, particularly reducing body weight and BMI through changes in eating habits and increasing physical activity, can lower the risk factors associated with obesity-related diseases, such as coronary heart disease (Całyniuk et al., 2016). Accordingly, the weight loss industry, recognizing obesity as a disease, is continuously growing. Various methods have been used to lose weight and reduce the risk of chronic diseases. Due to fewer side effects, behavioural and dietary modifications and increased exercise are considered the first treatment options for weight loss in obese patients. Drug therapy is recommended for patients who do not respond to lifestyle interventions alone, especially if bariatric surgery is not an option (Jackson et al., 2015). However, oral anti-obesity drugs are currently limited due to concerns about their efficacy and drug resistance (Tak and Lee, 2021).

Clinicians urgently require drugs that facilitate efficient weight loss. HSG4112, a structural analogue of glabridin, has a novel anti-obesity mechanism. The results of the anti-obesity trial, which includes HSG4112 as a primary indicator for anti-obesity treatment, along with the anti-inflammatory trial of HSG4112, confirmed that HSG4112 not only effectively reduces body weight but also improves inflammation, thereby promoting fat metabolism as an anti-obesity agent. Furthermore, it has been determined through safety and pharmacological testing that HSG4112 does not impact the central nervous, respiratory, and cardiovascular systems (Choi et al., 2021).

Several phase I trials were conducted to confirm that HSG4112 was safe and drug-resistant in humans. The results are as follows:

In the HSG4112-P1-01 trial, healthy male subjects were enrolled to evaluate the safety, tolerability, pharmacokinetic/pharmacodynamic characteristics, and food effect on HSG4112 following single and repeated oral administration. Safety and tolerance in all dosage groups were satisfactory.

In the HSG4112-P1-02 trial, healthy adult male subjects were enrolled to investigate the impact of food on the pharmacokinetic characteristics of HSG4112. The study involved a single-dose administration of HSG4112 and utilised a 3-way crossover design. Safety evaluation showed no clinically significant safety or tolerability-related issues; it was determined that the presence or absence of diet (fasting or fed condition) and type of diet (low-fat or high-fat diet) did not affect safety or tolerability.

The HSG4112-P1-03 study is ongoing to evaluate the safety of HSG4112 oral administration in 480 mg and 720 mg dosages in healthy and obese adult subjects, including female subjects. In the Part 1 study, the safety and tolerance in healthy adult female subjects were satisfactory. The Part 2 study is also ongoing in obese adult subjects.

## 2 Methods/design

### 2.1 Study design

This will be a randomised, double-blind, placebo-controlled, parallel-group trial. This study will be conducted over 16 weeks (intervention for 12 weeks) at five large hospitals in South Korea. Participants who are deemed eligible to participate in this study based on the inclusion/exclusion criteria will be assigned a subject number and randomly assigned to one of the four treatment groups. The experimental group was divided into 3 groups in proportion to the dose of HSG4112 compared to the placebo group, and a total of 4 groups were assigned with equal numbers to each group. Approximately 80 eligible participants will be recruited and divided into four groups. The flow diagram of the trial is shown in Figure 1.

**FIGURE 1 F1:**
[figure not shown]
Flow diagram of the trial.

### 2.2 Study population—sample size calculation

This study describes a phase 2a clinical trial to evaluate safety and efficacy after repeated administration of HSG4112. Subject sample size estimates for the primary efficacy endpoint are based on total body weight, assuming repeated measurements of body weight at baseline and every 4 weeks after that during the 12 weeks. Based on similar weight loss clinical trials with anti-obesity drugs, the covariance matrix of weight change over time is estimated to be AR(1) (sigma = 3.07, rho = 0.9). Therefore, if 20 subjects complete each administration group in this study, an average difference of 6 kg between HSG4112 and placebo administration can be derived with 80% power, assuming a two-sided significance level of 0.05. A difference of 6 kg is expected to be sufficient to assess the potential efficacy of HSG4112 treatment in this study. Therefore, this clinical trial’s target number of subjects per group was 20 (Muller and Curtis, 1989; Muller et al., 1992; Naik and Rao, 2001; Muller et al., 2007; Simpson et al., 2010).

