### 2.5 Randomisation, allocation concealment, and blinding

Upon completion of the run-in period, participants will be randomly assigned to one of four treatment groups—one group receiving placebo—in a ratio of 1:1:1:1. The randomisation procedure will be stratified using BMI by the order as follows: Randomisation No.: RX### (e.g., R1001)- X: BMI (<30 kg/m2 - 1, ≥30 kg/m2 - 2)- ###: Placement order of subject participating in this study

Allocation concealment will be maintained because no sealed envelopes will be opened during the study. Group assignments will not be disclosed or made available to participants and investigators throughout the study.

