### 2.8 Statistical analysis

The statistical analyses will be conducted by well-trained statisticians independent of the research team. Data will be analysed using intention-to-treat or per-protocol analyses. To compare the week 12 weight change from the baseline, each group will be analysed using the mixed model of repeated measures. A sensitivity analysis will be conducted using covariance analysis and model analysis. To compare the percentage change in body weight from baseline to the end of treatment, a logistic regression model will be used. Statistical *p*-value < 0.05 will be considered statistically significant. All analyses will be performed using the SAS software.

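### Read plainly, sigma = 3.07 with 20 completers per group gives over 99.9% power at 6 kg, not 80%; section 2.2 must define sigma and the contrast it powers

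*Protocol article*

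**What the plan says.** Section 2.2 of the protocol article gives one variance assumption, based on similar weight-loss trials: "the covariance matrix of weight change over time is estimated to be AR(1) (sigma = 3.07, rho = 0.9"). The design behind it is described as "assuming repeated measurements of body weight at baseline and every 4 weeks after that during the 12 weeks". The conclusion follows with a 'therefore': "if 20 subjects complete each administration group in this study", then "an average difference of 6 kg between HSG4112 and placebo administration can be derived with 80% power, assuming a two-sided significance level of 0.05". The section names no other SD, no multiplicity adjustment and no test statistic. It does not give a unit for sigma, and it does not say whether the 6 kg is a week 12 difference or an average over visits.

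Section 2.5 allocates participants "in a ratio of 1:1:1:1", so each dose is compared with placebo at 20 against 20. Section 2.8 sets the main comparison: "To compare the week 12 weight change from the baseline, each group will be analysed using the mixed model of repeated measures".

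**The concern.** The power is presented as a consequence of the listed inputs, and on their ordinary meaning it is not. In a covariance matrix described by a sigma and a rho, sigma is normally the marginal SD at each time. An SD near 3 kg with 20 per group detects a difference of slightly under 3 kg, less than half the 6 kg claimed.

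This paragraph is the article's only justification of the sample size and its only statement of what the trial can detect. If the SD of change is about 3 kg, a true effect of 3 to 5 kg is well within reach and a null result is informative against it. If the SD is about 7 kg, the same null result says little about effects below 6 kg. A reader cannot tell which case applies.

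**Working it through.** **Inputs.** From section 2.2: sigma = 3.07 (kg assumed), rho = 0.9, 20 completers per group, difference 6 kg, power 80%, two-sided 0.05, visits at baseline and weeks 4, 8 and 12. From section 2.8: week 12 change from baseline. From section 2.5: equal allocation.

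**Step 1. The plan's figure on the plain reading.**
- Standard error of a difference = SD × √(2/n) = 3.07 × √(2/20) = 0.971 kg.
- Noncentrality at 6 kg = 6 / 0.971 = 6.18.
- Power, noncentral t with 38 df: 0.99998. A simulation of the week 12 t test also gives 0.99998.
- The stated 80% is not reproduced.

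**Step 2. What the inputs do support.**
- Normal formula: (1.960 + 0.842) × 0.971 = 2.72 kg at 80% power.
- Noncentral t: 2.79 kg (38 df) or 2.75 kg (76 df, variance pooled over four groups). Simulated power at 2.8 kg is 0.803.
- Bonferroni, alpha 0.05/3: 3.27 kg at 80% power; power at 6 kg is 0.9998.
- For 6 kg, 5 per group gives 0.77 power and 6 per group gives 0.86.

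**Step 3. The SD that 6 kg at 80% would need.** With n = 20, the normal formula gives 6 / (2.802 × √0.1) = 6.77 kg, and the t distribution with 38 df gives 6.60 kg. The latter is 6.60 / 3.07 = 2.15 times the stated sigma.

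**Step 4. Other readings of sigma and of the contrast** (t, 38 df, 20 per group).

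| Reading | SD used (kg) | Power at 6 kg | 80%-power difference (kg) |
|---|---|---|---|
| 3.07 is the SD of raw weight; change SD = 3.07 × √(2(1 − 0.9³)) | 2.26 | >0.9999 | 2.05 |
| 3.07 is the marginal SD; mean of weeks 4, 8, 12: 3.07 × √0.9133 | 2.93 | >0.9999 | 2.67 |
| 3.07 is a variance: √3.07 | 1.75 | >0.9999 | 1.59 |
| 3.07 is the SD of each 4-week change; sum of three: 3.07 × √8.22 | 8.80 | 0.556 | 8.00 |
| 3.07 is the innovation SD: 3.07 / √(1 − 0.81); week 12 | 7.04 | 0.747 | 6.40 |
| Innovation SD; mean of weeks 4, 8, 12: 7.04 × √0.9133 | 6.73 | 0.784 | 6.12 |
| Innovation SD; mean of all four times: 7.04 × √0.8811 | 6.61 | 0.799 | 6.01 |

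Here 0.9133 = (3 + 4×0.9 + 2×0.81)/9 and 0.8811 = (4 + 6×0.9 + 4×0.81 + 2×0.729)/16 are the mean entries of the 3×3 and 4×4 AR(1) correlation matrices.

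With 76 df, the last three powers become 0.758, 0.795 and 0.809. With the normal formula they are 0.769, 0.805 and 0.819, and the two visit averages give n = 20.

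On the marginal reading, a four-group overall F test on the week 12 change gives at least 0.9997 when the largest difference from placebo is 6 kg.

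**The case against.** The strongest reply is that the article does not define sigma, and an AR(1) process can also be parameterised by its innovation SD. The marginal SD is then 7.04 kg. Section 2.2 speaks of an average difference and of repeated measurements, so a visit average is not foreign to the text. On that combination 6 kg, about 80% and 20 per group come out together. The calculation is also attributed to cited works and a fuller protocol that are not at hand and that may state the parameterisation.

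Part of this stands. A reader might infer that no reading yields 80%, and so that sigma, the difference or the power must be wrong, or that the assumed variance is too small by a factor of about 4.6 (2.15²). The document does not support either statement, because one reading nearly reproduces the figure and the detectable difference moves from 1.6 to 8.0 kg with the meaning given to sigma.

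It does not rescue the paragraph as written:
- Sigma is attached to a covariance matrix of weight change, and no innovation is mentioned.
- The closest match with 38 df, 0.799, averages in baseline, where change is zero by definition and no treatment difference can exist. The three post-baseline visits give 0.784.
- Section 2.8 compares groups at week 12, where this reading gives 0.747 to 0.758 by t.

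So even the favourable reading leaves sigma unlabelled and powers a contrast other than the one to be analysed.

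On importance, it is fair to say that nothing in conduct changes and that section 4 reports 81 participants already allocated.

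**Conclusion.** The point holds in this form: on the plain reading, the stated 80% power at 6 kg does not follow from the stated inputs. They give 0.99998 at 6 kg and 80% at about 2.8 kg (about 3.3 kg with Bonferroni). This assumes that sigma is the marginal SD of weight change in kg, with 20 completers per group and a two-sided 0.05 t test of one dose against placebo at week 12. The innovation-SD reading reaches about 78% to 81%, by t, only for a visit average, and about 75% to 76% for the week 12 contrast.

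A reader might also infer that 20 per group is too few. The calculation does not show that: on the plain reading the trial has more power than claimed. The error is in the justification. It still needs correcting, because the paragraph is the only statement of the trial's detectable effect and its meaning differs more than twofold between the two readings of sigma.

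**What to change.** Revise section 2.2 and leave the sample size unchanged:

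1. State whether sigma = 3.07 is the marginal or the innovation SD, and give its unit.
2. State the SD of the week 12 change, taken from the source trials.
3. Restate the power, or the detectable difference, for the week 12 dose-versus-placebo contrast of section 2.8.

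If 3.07 kg is the marginal SD, the text could read: *20 completers per group give about 80% power for a 2.8 kg difference and over 99.9% power for 6 kg at week 12.* If it is the innovation SD: *the week 12 change has an SD of about 7.0 kg, and 20 completers per group give about 75% power for 6 kg.*

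An SD of about 6.6 kg should not be inserted merely because it returns 80%; the SD has to come from the source data. The cost is one reworded paragraph and a look back at the original calculation. Enrolment, conduct and analysis are unaffected.

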### 2.3 Study population—inclusion/exclusion criteria

The study population will be adults aged between 19 and 70 years. We will recruit adults with a BMI between 30 and 39.9 kg/m^2^ (obese) with or without comorbid conditions or a BMI between 27 and 29.9 kg/m^2^ (overweight) with at least one documented treated or untreated comorbid condition (e.g., hypertension, dyslipidaemia, cardiovascular disease, glucose intolerance, and sleep apnoea). Other detailed inclusion and exclusion criteria are described in the Supplement.

### 2.4 Recruitment and screening

Participants will be recruited using advertisements and posters in five centres, nearby areas, and online. This study will be described briefly in advertisements and posters, along with the investigator’s contact information.

Potential participants will receive detailed information about the study and have informed discussions with a trained research coordinator. After signing an informed consent form, those who wish to participate are assessed. The screening test will include the participant’s height, weight, vital signs, 12-lead ECG, and laboratory tests. Participants who meet the eligibility criteria will begin a 2-week single-blind run-in period after the screening period. During this period, participants must consume a placebo to determine whether they comply with diet and lifestyle guidelines.

### 2.5 Randomisation, allocation concealment, and blinding

Upon completion of the run-in period, participants will be randomly assigned to one of four treatment groups—one group receiving placebo—in a ratio of 1:1:1:1. The randomisation procedure will be stratified using BMI by the order as follows: Randomisation No.: RX### (e.g., R1001)- X: BMI (<30 kg/m2 - 1, ≥30 kg/m2 - 2)- ###: Placement order of subject participating in this study

Allocation concealment will be maintained because no sealed envelopes will be opened during the study. Group assignments will not be disclosed or made available to participants and investigators throughout the study.

### 2.6 Intervention

In accordance with the study protocol, participants will be randomly assigned to double-blind treatment groups and receive a once-daily oral dose of the investigational product (IP) for 12 weeks. Participants in the four treatment groups will take three tablets daily as follows:• 1st group: HSG4112 200 mg (1 tablet of HSG4112 and 2 tablets of placebo)• 2nd group: HSG4112 400 mg (2 tablets of HSG4112 and 1 tablet of placebo)• 3rd group: HSG4112 600 mg (3 tablets of HSG4112)• 4th group: placebo (3 tablets of placebo)* Each HSG4112 tablet includes 200 mg of HSG4112.

The tablets will be dispensed and retrieved by trained research coordinators. The principal investigator and research coordinator will be responsible for storing and maintaining records of the test and placebo products.

### 2.7 Efficacy and safety assessment

The body weight and obesity/metabolism-related parameters will be evaluated to assess the efficacy of HSG4112. Assessments including measurement of vital signs, 12-lead ECG, clinical laboratory tests, pregnancy tests, physical examination, and adverse event monitoring will be performed to evaluate the safety and tolerability of HSG4112. Blood samples will be collected for pharmacokinetic assessment. In addition, samples from participants who have signed consent forms for exploratory genetic research will be analysed to detect polymorphisms in the PON2 gene. A summary of the schedule and all measurements that would be performed, is presented in Table 1.

**TABLE 1 T1:** Schedule of data collection (* Annotations 1–19: Detailed information is described in the Supplementary Data sheet S1).

Assessed items	Screening	Run-in	Intervention			End of Intervention^1^	Follow-up^1^
	Week −4 to −2 (Day −28 to −14)	Week −2 (Day −17 to −14)	Day 1 (Baseline)	Week 4 (Day 28 ± 3)	Week 8 (Day 56 ± 3)	Week 12 (Day 84 ± 3)	Week 16 (Day 112 ± 3)
Visit	1st^2^	2nd	3rd	4th	5th	6th	7th
Informed consent	O						
Eligibility assessment	O		O				
Demographic information	O						
Randomization^3^			O				
Dispensation of IP/placebo^4^		O	O	O	O		
Restitution of IP/placebo^4^			O	O	O	O	
Distribution of Diet/Physical activity diary^5^		O	O	O	O		
DEXA^6^			O			O	
Body weight	O	O	O	O	O	O	O
BMI^7^	O		O	O	O	O	O
Questionnaire (IWQOL-Lite-CT)			O			O	
Anthropometrics^8^	O		O		O	O	
Adverse events and Concomitant drug	O	O	O	O	O	O	O
Physical examination^9^	O		O	O	O	O	O
Vital sign^10^	O	O	O	O	O	O	O
12-lead ECG	O		O		O	O	
Clinical laboratory tests^11^	O		O	O	O	O	
Drug abuse test^12^	O						
Serum TSH	O						
Serologic test^13^	O						
Pregnancy test^14^	O		O	O	O	O	
Sex hormone test^15^	O		O		O	O	
Genotyping sampling^16^			O				
Pharmacokinetic sampling^17^			O	O	O	O	
Pharmacodynamic sampling^18^			O		O	O	
Body composition measurement^19^			O	O	O	O	

The primary outcome will be as follows:

• Change in Body Weight (kg) from Baseline to End of Treatment.• Evaluation of safety and tolerability by monitoring adverse events (number of adverse events, adverse drug reactions, serious adverse events, and suspected unexpected serious adverse reactions).

The secondary outcome will be as follows:

• Percentage of Participants with ≥5% Body Weight Loss from Baseline to End of Treatment.• Percentage of Participants with ≥7.5% Body Weight Loss from Baseline to End of Treatment.• Percentage of Participants with ≥10% Body Weight Loss from Baseline to End of Treatment.• Percentage change in body weight from baseline to the end of treatment.

Additional exploratory analysis and safety analysis will be conducted.

### 2.8 Statistical analysis

The statistical analyses will be conducted by well-trained statisticians independent of the research team. Data will be analysed using intention-to-treat or per-protocol analyses. To compare the week 12 weight change from the baseline, each group will be analysed using the mixed model of repeated measures. A sensitivity analysis will be conducted using covariance analysis and model analysis. To compare the percentage change in body weight from baseline to the end of treatment, a logistic regression model will be used. Statistical *p*-value < 0.05 will be considered statistically significant. All analyses will be performed using the SAS software.

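### Section 2.8 assigns logistic regression to percentage weight change, a continuous secondary outcome, without defining a cut-off or ordinal form

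*Protocol article*

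**What the plan says.** Section 2.7 of the protocol article lists four secondary outcomes. Three are proportions of responders, at losses of at least 5%, 7.5% and 10%; the strictest of them reads "Percentage of Participants with ≥10% Body Weight Loss from Baseline to End of Treatment". The fourth is a separate item: "Percentage change in body weight from baseline to the end of treatment".

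Section 2.8 names these methods:

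- for the primary outcome: "To compare the week 12 weight change from the baseline, each group will be analysed using the mixed model of repeated measures";
- as a supplement: "A sensitivity analysis will be conducted using covariance analysis and model analysis";
- for the fourth secondary outcome: "To compare the percentage change in body weight from baseline to the end of treatment, a logistic regression model will be used".

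The last sentence names its outcome in almost the same words as the fourth item of section 2.7. The article nowhere defines a threshold, a set of categories or an ordered version of percentage change.

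**The concern.** The method and the outcome do not fit. Logistic regression models the probability of a category, whereas percentage weight change is a measured, signed quantity. The outcomes that logistic regression suits, the three responder proportions, do not appear in section 2.8.

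At stake is what counts as pre-specified. Someone following the text would have to choose a cut for percentage change, and nothing in the article prevents that choice being made after the data are seen. Someone who silently used a linear model instead would depart from the published plan. With about 20 participants per arm, the information lost by dichotomising is also not trivial.

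**Working it through.** The article gives no figure for this analysis, so there is none to reproduce. The check compares the two sections and then illustrates the cost.

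**1. Outcomes against methods**

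| Outcome (section 2.7) | Type | Method named in section 2.8 |
|---|---|---|
| Weight change in kg (primary) | continuous | mixed model for repeated measures |
| Loss of at least 5% | binary | none named |
| Loss of at least 7.5% | binary | none named |
| Loss of at least 10% | binary | none named |
| Percentage weight change | continuous | logistic regression |

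The one method for binary data is attached to the one secondary outcome that is not binary.

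**2. What the literal reading requires**

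Let W0 be baseline weight and W12 weight at the end of treatment, which Table 1 places at week 12. Percentage change is D = 100 × (W12 − W0)/W0. An ordinary logistic model needs an indicator Y = 1 when D ≤ −c, for some cut c.

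- If c is 5, 7.5 or 10, Y is exactly one of the listed responder outcomes, and the fourth endpoint adds nothing.
- If c is anything else, it is a cut that the article neither states nor justifies.

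**3. Illustration of the power lost**

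Inputs: 20 per arm (section 2.2) and two-sided alpha 0.05 (sections 2.2 and 2.8). The article gives no means or SD on the percentage scale, so these are assumed and varied.

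Continuous analysis: two-sample t test with 38 degrees of freedom and noncentrality δ/(SD × √(2/20)). For means of −2% and −5% and SD 3.5, this is 3/(3.5 × 0.316) = 2.71, and power is 75%.

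Dichotomised analysis: with D normal, the responder probability is p = Φ((−c − mean)/SD). At c = 5:

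- placebo: Φ(−3/3.5) = 0.196; active: Φ(0) = 0.500;
- mean of the two: 0.348; difference: 0.304;
- standard error under the null: √(2 × 0.348 × 0.652/20) = 0.151;
- standard error under the alternative: √((0.196 × 0.804 + 0.500 × 0.500)/20) = 0.143;
- power: Φ((0.304 − 1.96 × 0.151)/0.143), about 53%.

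The same steps for the other cuts and assumptions give:

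| Assumed means (placebo, active); SD | Continuous | Cut 5% | Cut 7.5% | Cut 10% |
|---|---|---|---|---|
| −2%, −5%; 3.5 | 75% | 53% | 36% | 17% |
| −1%, −4%; 3.5 | 75% | 47% | 27% | 12% |
| −1%, −4%; 4.5 | 54% | 34% | 25% | 15% |

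Across these cases the 5% cut costs 20 to 28 percentage points of power, and the 10% cut costs 39 to 63. The two-proportion formula is a normal approximation and is rough where responders are few, so the table shows direction and rough size only.

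**The case against.** The strongest reply is that this is a drafting slip. The sentence probably merges the responder items, which also begin with a percentage, with the percentage-change item, and logistic regression was meant for the responders. That is plausible, but the article does not say so. Section 2.8 names the continuous outcome, and a reader cannot tell which analysis was fixed in advance. The reply lowers the severity; it does not remove the mismatch.

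Three stronger readings are tempting, and the document does not support them.

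- *That percentage change cannot be analysed by any logistic model.* A cumulative-logit model can be fitted to an ordered continuous outcome without a cut. The article specifies no such model, so the form remains undefined, but impossibility would be too strong a claim.
- *That the responder outcomes have no planned analysis.* An article may leave that to the full protocol or the SAP, neither of which is shown. The gap matters here only as the other side of the misplaced method.
- *That logistic regression would often break down for want of placebo responders.* The article does not commit to maximum likelihood with Wald tests, and the size of the problem depends on an uncertain SD. Assume a 90 kg baseline and a 2 kg placebo loss, neither of which is in the article. Taking sigma = 3.07 kg as the SD of week-12 change, a 10% loss has probability Φ((2 − 9)/3.07) = 0.011, and the chance of no such responder among 20 is 0.989^20, about 80%. But section 2.2 says that with 20 per group "an average difference of 6 kg between HSG4112 and placebo administration can be derived with 80% power, assuming a two-sided significance level of 0.05". In a plain two-group t test, 80% power would need an SD of about 6.6 kg. The responder probability is then Φ(−7/6.6) = 0.144, and the chance of none is 0.856^20, about 4%. A result that moves from 80% to 4% on an undefined input supports no conclusion, and the choice of fitting method belongs in the SAP.

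**Conclusion.** The point holds as a misassignment: section 2.8 gives a method for categorical data to a continuous secondary outcome, with no cut-off or ordinal form that would make it workable. This rests on the wording of sections 2.7 and 2.8 alone. The power figures only illustrate the cost, and they depend on assumed means and SDs, on normality, and on the analyst resolving the sentence by dichotomising.

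Severity is moderate. A reader might infer that the trial's main efficacy conclusion is at risk. It is not: the primary change in kg has a suitable repeated-measures model, and the error is confined to secondary endpoints. Nor does the article show that the sponsor intends to dichotomise; it shows only that the published text does not fix an analysis of percentage change that can be followed as written.

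**What to change.** Replace the sentence in section 2.8 with two:

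- Percentage weight change is analysed with the mixed model for repeated measures used for the primary outcome, or by covariance analysis at week 12, and reported as the mean difference from placebo with a 95% CI for each dose.
- Logistic regression is used for the proportions losing at least 5%, 7.5% and 10%.

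Table 1 schedules body weight at baseline and weeks 4, 8 and 12, so the mixed model needs no further data. Both continuous-outcome methods are already named in section 2.8, and all are routine in SAS. The cost is two sentences, repeated in the SAP if it carries the same wording.

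Section 4 reports that 81 participants have already been allocated, so the correction should be dated and made before unblinding. If unblinding has already taken place, the report should say so and state which analysis had been fixed beforehand.
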